#### 2.5.2. Secondary Outcomes

##### Preliminary Efficacy

The secondary aim of this study is to assess preliminary efficacy of the TK-MT on health outcomes. Preliminary intervention efficacy outcomes are changes in health behaviors (cooking and eating behaviors, physical activity, sleep quality, overall health, and behavior change); anthropometric measures (BMI, blood pressure, and waist circumference); and biometric measures (glycemic control, lipid metabolism, and liver function). 

Self-reported questionnaires, laboratory data (blood), and body anthropometrics (weight, height, BMI, waist circumference, blood pressure) will be collected at baseline, 4, 12, and 18 months. These data will be entered into REDCap and analyzed to assess for changes from baseline to assessment timepoints (see Table 5).

##### Behavior Changes

Cooking and Eating Behaviors

The Teaching Kitchen (TK) Core Survey is a 28-item questionnaire designed to assess self-reported eating habits, cooking habits, cooking frequency, food acquisition habits, meal planning habits, confidence related to purchasing, planning, preparing meals, and physical activity behaviors. This survey comprises modified survey items from a variety of sources including the Exercise Vital Sign (EVS) screener [49], the Cooking With Chefs (CWC) cooking confidence scale [50], and the Gallup cooking frequency questionnaire [51].

Mindful eating will be assessed using 25 of the 28 items from the mindful eating questionnaire (MEQ) [52]. The MEQ evaluates feelings of disinhibition, awareness, external cues, emotional response, and distraction related to food and eating [52]. There is strong confidence in the MEQ to assess mindful eating constructs in U.S. adults with varying BMIs [52]. Diet quality will be assessed using the 27-item Prime Diet Quality Score 30-day food frequency screener (PDQS-30D) [53]. The PDQS-30D quickly provides a diet quality score based on self-reported food consumption over the past 30 days [53]. The PDQS-30D has been assessed for concurrent validity against the Automated Self-Administered 24-Hour Dietary Assessment Tool (ASA24) [54] and the Healthy Eating Index (HEI) 2015 [55,56] metrics in adult women in the United States [53] (see Table 5).

Cooking self-efficacy will be measured using an original tool developed by the UTH team to assess participants’ perceived confidence to overcome barriers in preparing and consuming healthy meals. The self-efficacy tool has been preliminarily tested through the generation of a 40-item pool and reviewed by researchers in the nutrition and behavioral theory field. Items have been ranked for final inclusion in the self-efficacy scale (11 items). A bipolar 5-point Likert scale has been chosen to capture “how confident” respondents are to consume and prepare healthy meals despite facing barriers where 1 indicates “not at all confident” and 5 indicates “extremely confident”, with all points labeled to reduce ambiguity. Furthermore, a neutral option has been included to help understand if respondents’ self-confidence is “neutral” regarding certain statements.

Lifestyle Behaviors

Changes in physical activity will be assessed at baseline and all follow-up points using the International Physical Activity Questionnaire (IPAQ) [57]. IPAQ is a validated tool that assesses physical activity levels across various domains (e.g., work, leisure, transportation) [57]. Weekly changes in physical activity will be assessed during the weekly participation REDCap survey using 2 items from the EVS [49]. The American Psychology Association (APA) Diagnostic and Statistical Manual of Mental Disorders 5th Edition (DSM5) sleep quality questionnaire will be used to assess participants’ sleep quality and patterns, including sleep duration, sleep onset latency, and sleep efficiency [58]. It will be administered at baseline and all follow-up points to examine potential changes in sleep habits. The RAND 20-Item Short Form Health Survey (SF-20) is a well-established survey that will be administered at baseline and follow-up points to assess participants’ overall health status, including physical and mental components [59]. It will provide a comprehensive overview of participants’ health-related quality of life. The University of Rhode Island Change Assessment (URICA) measures readiness to change in various health behaviors, including diet and exercise [60]. It will be administered at baseline and post-intervention to assess changes in participants’ motivation and commitment to adopting healthier habits.

##### Laboratory Data

Fasting blood glucose, fasting insulin, hemoglobin A1c, ALT, and AST (collected as a hepatic panel), and fasting lipid profile (total cholesterol, triglycerides, HDL, and LDL) will be collected by venipuncture at baseline, 4, 12, and 18 months. Data will be collected at affiliated or at independent laboratories. All laboratory data collections will be conducted according to SOPs regardless of study site or collection location. Once lab results are received by the study team, staff will enter the data into the REDCap laboratory data form (see Table 5), which will be reviewed by the site medical director. Participants will be notified of any concerning values and given a letter to discuss with their primary provider. Study teams will assist in this communication (see Table 5).

##### Anthropometrics

Weight, height, BMI, blood pressure, and waist circumference measurements will be collected at baseline, 4, 12, and 18 months by a trained member of each study team using calibrated equipment in a lab or clinic setting following this study’s outlined standard operating procedures (SOPs). Collected measurements will be entered into the REDCap anthropometrics form by research staff (see Table 5).

**Table 5 nutrients-17-00314-t005:** Secondary Efficacy Outcomes of the Teaching Kitchen Multisite Trial.

Indicator	Assessment Tool	Description
Cooking behaviors		
Δ Cooking and eating habits	TK Core Survey	28 items assessing eating habits, cooking habits, cooking frequency, food acquisition habits, confidence r/t food acquisition, meal planning, and cooking
Δ Cooking skills self-efficacy	Cooking Self-Efficacy Survey	11 items assessing cooking confidence and self-efficacy
Lifestyle behaviors		
Δ Diet intake	PDQS-30D [53]	27 items assessing foods/beverages consumed over the past month
Δ Mindful eating	MEQ [52]	28 items assessing mindful eating
Δ Physical activity	IPAQ [57]	7 items assessing physical activity type, frequency, and duration
Physical activity frequency Physical activity duration	EVS	Weekly assessment of changes in physical activity type, frequency, and duration
Δ Sleep habits	PROMIS APA DSM5 [58]	8 items assessing sleep quality
Δ Physical health	URICA [60]	12 items assessing readiness to change r/t physical health
Δ General health	CDC Healthy Days Measures [61]	5 items assessing physical health, mental health, overall health, and smoking habits
Δ Quality of Life	RAND 20 SF [59]	20-Item Short Form Health, quality of life, quality of work–life balance survey
Laboratory Measures		
Δ Glycemic function	Fasting serum glucose [62,63]	Measure of glucose circulating in serum while in a fasted state
	Fasting serum insulin [64]	Measure of insulin circulating in blood while in a fasted state
	Hemoglobin A1C	Estimate of average glucose concentration in blood over the past 120 days
Δ Liver function	Aspartate transaminase (AST) Alanine transaminase (ALT)	Markers of hepatocellular injury
Δ Lipid profile	Total cholesterol High-density lipoprotein Low-density lipoprotein Triglycerides	
Anthropometric Measures		
ΔBMI	BMI = weight (kg)/height (m)^2^	Change in anthropometric measures at 4, 12, and 18 months
Δ Blood pressure	Electric blood pressure monitors	
Δ Waist circumference	Measuring tape performed by trained staff	

Δ = change in.

### 2.6. Intervention Implementation

Another secondary aim will be to identify barriers and facilitators of implementation. Qualitative assessments will occur though open-ended questions on staff and participant feedback surveys and through semi-structured interviews with intervention participants. Participant interviews will be conducted at the 12-month assessment timepoint. Interviews will assess acceptability, usefulness, strengths, weaknesses, compliance, and missing elements of this study, intervention curriculum, and intervention delivery. A trained study team member will conduct and record audio of each interview for transcription. Interviews will take place via phone, video call (voice only), or in-person. All participant data will be de-identified. Open-ended survey questions will also be included in participant satisfaction surveys.

Open-ended staff surveys will evaluate barriers and facilitators to meeting participant needs, perceived need for innovation, and participant feedback.

### 2.7. Data Analysis

The primary outcome of feasibility will be assessed through frequency data that are collected on recruitment, attendance, and fidelity. Descriptive statistics (proportions for rates, means, or medians for satisfaction scores) will be used to summarize these measures. We will also document reasons for non-completion (withdrawal or attrition). For surveys addressing participant satisfaction, descriptive statistics (means, medians, proportions, 95% confidence intervals [CI]) will be computed, and data will be analyzed to assess for change over the 16-week intensive curriculum, 8-month boosters, and 18-month sustainability measures. A paired *t*-test will evaluate pre/post changes in continuous measures. 

Secondary associations considering participation in the TK-MT and the biometric data (change in body weight and clinically relevant change in one of the following metabolic markers: fasting plasma concentrations of glucose, insulin, triglyceride, cholesterol, HDL, LDL, and liver function as AST and ALT) will be analyzed using a linear mixed-effects regression model for continuous outcomes. 

Descriptive statistics (means, medians, proportions) will be used to summarize baseline characteristics and changes in these outcomes (self-reported health behaviors, lab values, and anthropometrics) over time. Baseline and demographic data will be controlled for in this model. Lastly, we will investigate whether missing data, due to dropouts and poor attendance, are non-ignorable through a sensitivity analysis based on the imputation approach developed by co-investigator [name] and colleagues [65]. Preliminary investigation of associations and correlations will be explored graphically and formally using parametric and nonparametric tests, as appropriate. Regression diagnostics will be performed to assess the validity of the multivariate models and their assumptions, and first-order interaction terms will be included to assess potential effect modification. 

For participant interviews and open-ended survey items, thematic analysis will be conducted by the HSPH team to independently read transcripts and conduct open and then focused coding using inductive and deductive coding approaches in NVivo (15, Lumivero, Denver, CO, USA) [66].

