### 2.2. Study Setting

Eligible study sites will have a functioning teaching kitchen [42] with facilities that can accommodate up to 30 participants for hands-on cooking activities. Sites must have a core team with the expertise to deliver the TK-MT protocol: a primary investigator (PI) to lead the site-level team; a medical doctor (MD) to confirm clinical eligibility and provide medical oversight during the study; subject matter experts (SMEs) in culinary arts, nutrition education, exercise science, mindfulness training, and health coaching to facilitate class sessions; and research staff and infrastructure to conduct the clinical trial.

The TK-MT is being conducted at four U.S. academic institutions within the Teaching Kitchen Collaborative (TKC) [43] network; Dartmouth Health (DH), a rural academic medical center serving Northern New England; the University of Texas Health Science Center Houston (UTHealth Houston) School of Public Health, an urban, public university in the southwest United States, and two urban, public universities in the western United States—University of California, Irvine (UCI), and University of California, Los Angeles (UCLA). The Harvard T.H. Chan School of Public Health (HSPH) is serving as the coordinating center.

The coordinating center will oversee the conduct of the study, compliance with IRB regulatory matters, distribution of curriculum materials, maintenance of consistent data collection, and the conduct of regular primary investigator and study team meetings. HSPH will conduct power analysis, direct participant randomization, and provide overall data management and data analysis. Data will be securely stored in password-protected REDCap (14.5.25, Vanderbilt University, Nashville, TN, USA) databases maintained by each individual study site; de-identified data will be shared with the coordinating center for network-wide analyses.

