#### 2.3.2. Sample Size Estimation

A proposed sample size of 320 participants (4 study sites × 2 cohorts × 20 participants per arm) will have 80% power to detect significant improvements in metabolic syndrome biomarkers ranging from 14.2 to 30.15%, assuming that control group participants have improvements ranging from 5 to 15% for ɑ = 0.05 by using a two-sample *t* test. Power analysis calculations for sample size are based on reported effect size estimates of metabolic syndrome markers (Appendix A) [44].

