#### 2.3.3. Recruitment and Randomization

Potential participants will be recruited through the TK-MT website, paid social media advertisements, physical and digital flyers, social media postings, institutional emails, television spots, ads in community newspapers, booths at health fairs, and referrals from research or clinical staff at the study sites. Study recruitment will follow the process outlined in Figure 1. Preliminary study eligibility will be assessed through an optional pre-screening survey on the TK-MT website followed by a screening phone call.

Alternatively, interested individuals can call the study team directly and complete a phone call screening. Those who are likely eligible based on the phone call screening will complete a follow-up video call with a trained research assistant (RA). These screening methods will collect eligibility data and visually confirm minimal operating kitchen equipment described in the inclusion criteria. The RA will explain the study details and obtain informed consent during these screening calls. Final eligibility will be confirmed by study site PI based on a review of anthropometric data, laboratory data, self-reported medication lists, and study site MD recommendations.

Eligible participants will be randomized at the site level in blocks to either the TK-MT intervention group or the wait-list control group receiving standard care (i.e., followed as usual by their primary care physician). Each site will independently enroll 1–2 cohorts and randomize 28–48 participants to each study arm (for single-cohort sites) or 14–30 participants per arm (for double-cohort sites); the wait-list control group will receive a condensed version of the intervention curriculum after completing the 12-month assessments. Individuals who share a household can participate in this study only if they have separate kitchen workspaces for virtual classes and must be randomized to the same study arm. All recruitment and randomization data will be documented in site-specific REDCap surveys and forms. Incentives, in the form of gift cards and small gifts (notepad, measuring spoons, etc.) valued at a total of USD 200 per individual will be provided after completing (1) laboratory and anthropometric screening, (2) baseline psychometric assessments, (3) 4-month assessments, (4) 12-month assessments, and (5) 18-month assessments.

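### Randomisation is blocked within site, but section 2.7 names neither site nor cohort in the secondary efficacy model; adding them is a small, nearly free improvement

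*Protocol article*

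**What the plan says.** **Allocation.** Section 2.3.3 of the protocol article states: "Eligible participants will be randomized at the site level in blocks to either the TK-MT intervention group or the wait-list control group". Section 2.2 gives the number of sites: "The TK-MT is being conducted at four U.S. academic institutions". Site is therefore the randomisation stratum. Each site runs one or two cohorts, and people who share a household "must be randomized to the same study arm".

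**Efficacy model.** Section 2.7 says that the biometric outcomes "will be analyzed using a linear mixed-effects regression model for continuous outcomes". On covariates it says: "Baseline and demographic data will be controlled for in this model". Section 2.5 lists the sociodemographic items as age, gender, race, ethnicity, income and education. Section 2.7 does not mention site or cohort and does not give the random-effects structure.

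**Status and sizing.** Section 2.5.1 makes feasibility the primary aim, and section 2.5.2 makes preliminary efficacy secondary. The sample size of 320 (section 2.3.2 and Appendix A) comes from an unstratified two-group comparison.

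**The concern.** When allocation is balanced within site, the difference between arms is free of between-site variation. An analysis that includes site uses this. An analysis without site counts the between-site variation as residual noise and reports a standard error somewhat larger than the true one. Confidence intervals are then slightly wide, and the nominal 5% test runs slightly below 5%.

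Site may well matter here. The introduction stresses different populations, section 2.2 describes one rural centre and three urban universities, and each site's own staff take the anthropometric measurements. Section 2.7 names the model class, covariates, interaction terms, diagnostics and a missing-data sensitivity analysis, but not the one factor that the randomisation fixes. An analysis could follow that text to the letter and leave site out. What is at stake is some precision in a secondary analysis, not bias.

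**Working it through.** **1. The plan's own figure.** Inputs from Table A1: 160 per arm, two-sided 0.05, two-proportion test with pooled variance under the null. Power = Φ{[(p2 − p1) − 1.96·√(2·p̄(1−p̄)/160)] / √([p1(1−p1) + p2(1−p2)]/160)}.

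| Control | Intervention | Power |
|---|---|---|
| 5% | 14.2% | 80.1% |
| 10% | 21.4% | 80.3% |
| 15% | 27.9% | 80.6% |

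The 1:1, 80% entries reproduce. They are unstratified, so nothing below changes them.

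**2. Assumptions for the site effect.** The documents give no between-site variance. Let f be the share of a continuous outcome's variance that lies between sites, and take f = 1%, 2%, 5% and 10%. Assume 1:1 allocation within site and a total SD of 1. Where baseline is in the model, assume a within-site correlation of 0.6 between baseline and outcome.

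**3. Standard error without site divided by standard error with site.**

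- (a) No baseline in the model: 1/√(1−f).
- (b) Baseline in the model, same site shift at baseline and follow-up: √{[1 − (0.6 + 0.4f)²] / [0.64(1−f)]}.
- (c) Baseline in the model, site shift at follow-up only: √{[0.64(1−f) + f] / [0.64(1−f)]}.

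| f | (a) | (b) | (c) |
|---|---|---|---|
| 1% | 1.005 | 1.001 | 1.008 |
| 2% | 1.010 | 1.002 | 1.016 |
| 5% | 1.026 | 1.006 | 1.040 |
| 10% | 1.054 | 1.012 | 1.083 |

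Simulations of four sites of 80 agree. Inflation in case (b) was 0.1/0.2/0.6/1.3% with fixed site effects, and 0.1/0.2/0.5/0.9% with site effects drawn at random. In case (c) it was 0.8/1.6/4.1/8.4%.

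**4. Test level and power in case (a).** An effect of (1.960 + 0.842)·√(2/160) = 0.313 SD has 80% nominal power. The reported standard error is √(2/160) and the true one is √((1−f)·2/160).

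| f | True level without site | Power without site | Power with site |
|---|---|---|---|
| 1% | 4.9% | 80.1% | 80.4% |
| 2% | 4.8% | 80.2% | 80.8% |
| 5% | 4.4% | 80.6% | 82.0% |
| 10% | 3.9% | 81.3% | 84.0% |

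The forgone gain is 0.3 to 2.7 points. Power without site never falls below 80%.

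**5. A component that acts the other way.** The intervention arm is taught in groups of about 20 (Appendix A). If correlation ρ within a class group is unmodelled, true/reported standard error = √[(1 + 1 + 19ρ)/2]. This is 1.05, 1.09 and 1.21 for assumed ρ = 0.01, 0.02 and 0.05. With site share and ρ each between 0.01 and 0.05, and both ignored, reported/true standard error = √{(2/160) / [(1−f−ρ)/160 + ρ/8 + (1−f)/160]}, which runs from 0.83 to 0.98. The reported standard error would then be too narrow overall.

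**The case against.** The strongest objection is that this rests on silence. Section 2.7 belongs to a condensed article. It does not say that the model adjusts for nothing else, and a mixed-effects model in a four-site trial may carry site as a random effect. That detail often sits in an analysis plan, which is not shown. This stands: a reader might infer that the analysis ignores the randomisation strata, but the text supports only that site and cohort are not named.

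A reader might also infer that the standard errors are too wide and the trial underpowered as a result. The documents do not support this either. Section 2.7 plans baseline adjustment, which removes most of a stable site difference. Planned power holds in every scenario above. Unmodelled class-group or household correlation could reverse the net direction.

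Several passages that might seem to show strong site effects are weak evidence:

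- Section 2.5.2 says of laboratory data: "Data will be collected at affiliated or at independent laboratories". It then places all collection under common procedures at every site.
- Grocery methods vary by site, but controls receive no groceries, so this bears on the treatment effect by site rather than on a difference shared by both arms.
- The arm-size ranges in section 2.3.3 apply to both arms and do not suggest drift from 1:1. The same-arm household rule could disturb balance slightly.
- An unstratified sample-size test is ordinary practice.

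One part of the objection does not carry. Baseline adjustment does not always make site negligible, because a site shift that arises only at follow-up is not captured by baseline (case c).

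**Conclusion.** The point holds as a minor, nearly free improvement, not as a demonstrated error. The stated adjustment set leaves out the factor used to block the randomisation. Fitting the model that way leaves the treatment estimate unbiased under within-site balance and makes that component of the standard error conservative. For an assumed site share of 1% to 10%, the inflation is about 0.5% to 5% without baseline, about 0.1% to 1% with baseline and stable site shifts, and up to about 8% with shifts at follow-up only. These figures rest on an assumed site variance, an assumed baseline correlation of 0.6 and 1:1 allocation within site. They describe the site component alone and say nothing about the net direction if other clustering is unmodelled. The analysis affected is secondary.

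**What to change.** In section 2.7, state that every between-arm efficacy model includes site as a fixed effect, with cohort within site where a site runs two cohorts, in addition to the outcome's baseline value and demographics. State that any yes/no comparison of marker improvement is adjusted for or stratified by site in the same way.

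The cost is a sentence or two and 3 degrees of freedom (4 sites − 1) to 7 (8 site-cohorts − 1) out of about 320. Site is already recorded for everyone, and no new data, participants or procedures are needed. The change also protects the arm comparison if balance within a site drifts. It does not deal with class-group or household correlation, which is a separate modelling question.
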